#### **11.9 Discontinuation of the study**

The study will be stopped if documentation clearly shows serious side effects related to DCS in two or more patients.

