#### ***Other possible reasons for premature discontinuation of treatment***

- Any serious adverse event or circumstances during the two days DCS administration justifying the discontinuation of the treatment in the investigator's opinion, if the serious adverse event is considered to be uniquely caused by DCS/placebo.
- Protocol deviation which jeopardizes the patient's safety.
- Patient lost to follow-up: When the participant discontinues reporting to the investigator, he/she must make an effort to contact the participant to establish the reason for discontinuation, and to suggest the participant comes to an end-of-study visit. If all such attempts to contact the participant fails, the investigator then declare the participant "lost to post-treatment assessment" and the investigator should document all these attempts in the corresponding medical file.

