## **10. DCS/ placebo side effects**

The DCS will be administrated in two single dosages, and the patients will be randomized to receive either 100 mg or 250 mg. Both dosages are smaller than standard dosage when the drug is administrated for its original purpose.

Previous trials with DCS with doses of 25-250 mg have reported little or no side-effects of DCS compared to placebo (11, 117-119). One potential danger could be that DCS would produce

reversed effects, i.e. DCS could enhance fear learning instead of fear extinction. One study reported facilitation of reconsolidation of fear if DCS was given prior to a single recall trial, but after using several recall trials, it facilitated extinction (120). No other published reports have reported any reversed effects of DCS.

In order to control for possible interactions with antidepressants (121) patients will be stratified in accordance to whether they receive antidepressants or not.

The DCS will be taken at the clinic, administered by a designated person, and the patients will be together with the therapist for at least five hours after intake. This ensures both compliance as well as the possibility to record side effects. Patients will be in contact with the clinic weekly for the first three weeks after the DCS/placebo intervention, which further ensures recording of side effects.

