### **11.3 Blinding and code breaking**

Sealed envelopes with the DCS/Placebo treatments will be sent from the Kragerø Tablet Production and given to the medical competent. The envelopes will be kept in a secured place and accessible to any person authorized to un-blind. A decoding list containing the treatment codes will be kept.

The code for any study participant should only be broken by the medical competent or authorized person if it is absolutely necessary to ascertain the type of treatment given. The circumstances under which the code may be broken are life-threatening emergencies, for which the choice of therapy may depend on the treatment received by the patient. If so, the medical competent must write his/ her name, signature, date, the number of the participant concerned and reason for breaking the code on the code envelope. All information concerning adverse drug reactions, drug interactions are given in the SPC [66]. The blinding will be broken after the 12 months follow-up. At the 5-year follow-up the assessors will be blinded for the randomization.

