### **12.3 Definition of Serious Adverse Events**

Each AE is to be classified by the investigator as serious or non-serious. Seriousness is not defined by a medical term; it is a result or an outcome. An AE is defined as a Serious Adverse Event (SAE) if it:

- results in death
- is life-threatening
- Requires inpatient hospitalization or prolongation of existing hospitalization
- results in persistent or significant disability/incapacity
- results in a congenital anomaly/birth defect

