### **12.4 Definition of Suspected Unexpected Serious Adverse Reactions**

Protocol No: 2013-002574-49

Date 09 September.2015

Version: 03

Each SAE that is at least possibly related to IMP is to be classified by the investigator as expected or unexpected. A SAE that is at least possibly related to IMP, and **unexpected**, is defined as a Suspected Unexpected Serious Adverse Reaction (SUSAR). It is expected if it is already known from earlier trials or is mentioned in relevant documents. The reference security information of the IMP can be found in the approved SPC (122).

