### **12.5.2 Assessment of Causality**

**Unlikely:** The event is most likely related to an etiology other than the IMP.

**Possible:** A causal relationship is conceivable and cannot be dismissed.

**Probably:** Good reason and sufficient documentation to assume a causal relationship.

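### Section 12.1 takes every SPC-listed side effect out of adverse-event reporting, serious ones included, so such an event could miss SAE recording and the section 11.9 stopping count

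*Protocol*

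**What the plan says.** Five parts of the protocol bear on this.

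- **11.9** sets the stop: "The study will be stopped if documentation clearly shows serious side effects related to DCS in two or more patients".
- **12.1** defines an adverse event broadly. It then names weariness, drowsiness, headache and tremor as known effects of DCS and says that side effects recorded in the SPC are not to be reported as adverse events. The reason given is that far larger doses have been used in tuberculosis and that this trial gives small doses on two days.
- **12.2** has the investigator classify each adverse event as related or unrelated to the product, with a reasonable possibility of association as the threshold. **12.5.2** adds three causality grades, the highest being "Good reason and sufficient documentation to assume a causal relationship".
- **12.3** has the investigator classify each adverse event as serious or not. The criteria include "Requires inpatient hospitalization or prolongation of existing hospitalization". It adds that seriousness depends on what the event led to, not on its medical name.
- **12.4** continues: "Each SAE that is at least possibly related to IMP is to be classified by the investigator as expected or unexpected". On what counts as expected it says: "It is expected if it is already known from earlier trials or is mentioned in relevant documents". The approved SPC is named as the reference.

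**The concern.** The exclusion in 12.1 has no limit by seriousness, while every later safety step starts from an adverse event. Relatedness (12.2), seriousness (12.3), intensity (12.5.1) and the form in the CRF (12.7.1) all attach to events that have first been reported as adverse events. Whatever 12.1 removes, the later steps do not see.

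SPC-listed reactions are also the ones most readily attributed to the drug, so the exclusion falls on the events that a stopping rule about drug-related harm most needs. At stake are the completeness of the serious-event record and the count in 11.9.

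**Working it through.** The protocol states no operating characteristic for 11.9, so there is no figure to reproduce. The check is of the text.

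**1. What reporting means here.** Section 12.7.1, under the heading on reporting of adverse events, consists of entering each event on an adverse-event form in the CRF. An effect that is not reported as an adverse event therefore gets no such form.

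**2. Scope of the exclusion.** It covers known side effects recorded in the SPC. The four effects named are given as examples, and nothing restricts the exclusion to mild or non-serious occurrences.

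**3. Seriousness.** Under 12.3 a serious adverse event is an adverse event plus an outcome such as hospitalisation. Because the outcome decides, even one of the four named effects is serious if it leads to admission. The gap therefore does not depend on whether the SPC lists any reaction that is serious in itself.

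**4. One event followed through.** Take a hypothetical patient admitted to hospital with a tremor judged related to the capsule.

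| Section | As 12.1 is written | As 12.4 assumes |
|---|---|---|
| 12.1, 12.7.1 | Listed effect, so no adverse-event form | Adverse event recorded |
| 12.3, 12.7.2 | Not an adverse event for reporting, so no SAE form | SAE recorded and sent to the principal investigator |
| 12.4 | Never reached | SAE, related, expected under the SPC |
| 12.7.3 | No report | No report, because an expected event is not a SUSAR |
| 11.9 | No required record from which to count it | Counts as one patient |

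The SUSAR route cannot catch the event, because an SPC-listed reaction is expected by definition. The SAE record is the only mandatory route, and 12.1 closes it.

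**5. Effect on the count.** The limit is 2 patients. If m patients with related serious events are left out because the event type is listed, the recorded count reaches 2 only when 2 + m patients have been affected.

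- m = 0: stop at 2.
- m = 1: stop at 2 + 1 = 3.
- All such events of a listed type: the recorded count stays at 0.

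No probability can be given for these cases, because the protocol states no serious-event rate.

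**The case against.** **The effects named in 12.1 are mild, and the SPC is not at hand.** It is true that the documents do not show whether the SPC lists a serious reaction. But the exclusion covers everything the SPC records, and under 12.3 the outcome makes an event serious, whatever it is called. The dose argument in 12.1 supports leaving out minor expected effects; it does not support leaving out an admission.

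**Side effects are watched for elsewhere.** Section 10 provides for observation after intake and weekly contact for three weeks, 11.10 uses an adverse-event questionnaire, and 13.1 summarises side effects. Section 11.9 itself speaks of side effects, not of SAEs. This stands in part: an admission would probably be noticed, so omission from the count is possible, not certain. But these provisions do not require the seriousness and causality classification that 12.2 and 12.3 attach to adverse events.

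**A stronger reading.** A reader might infer that 11.9 cannot work at all while the trial is blinded, because 11.3 says: "The circumstances under which the code may be broken are life-threatening emergencies, for which the choice of therapy may depend on the treatment received". The documents do not support that. The protocol uses DCS for the blinded capsule elsewhere, for example "The DCS will be taken at the clinic, administered by a designated person", and 12.2 gives the investigator a relatedness judgement that needs no code. Applied that way, 11.9 is workable and errs towards stopping. With 128 patients on DCS and 32 on placebo, and events unrelated to arm, two capsule-attributed events in different patients include at least one placebo patient with probability 1 − (128 × 127)/(160 × 159) = 0.361. The error is then a stop that was not needed, not a missed one. Requiring two confirmed DCS patients would raise the expected number of attributed events at the stop from 2 to 2/0.8 = 2.5 with no drug effect. If the rate on DCS were double, the DCS share would be 8/9 and the figure 2/(8/9) = 2.25. That is a trade-off for the sponsor.

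**Different causality thresholds.** A reader might also see a contradiction between the patient-level wording in 5.3, "if the serious adverse event is considered to be uniquely caused by DCS/placebo", and the looser threshold in 12.4. These serve different purposes and need not agree. Naming a grade in 11.9 would add clarity but corrects no error.

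**Conclusion.** The point holds and is minor. Section 12.1 is wrong as written: it has no exception for serious events, and it conflicts with 12.4, which presupposes that expected serious events are recorded and checked against the SPC. Followed literally, it removes such events from SAE recording and could leave them out of the 11.9 count. With a limit of two, each omission moves the stop back by one affected patient.

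This rests on two readings: that reporting in 12.1 means entry on the form described in 12.7.1, and that the exclusion applies to all occurrences of a listed effect. It assumes no event rate. The severity stays minor because exposure is two single doses under observation, qualifying events may never occur, and an investigator might well record an admission regardless of 12.1. Section 11.9 can be applied on blinded causality as it stands.

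**What to change.** - **12.1:** limit the exclusion to non-serious side effects listed in the SPC, and state that any event meeting a 12.3 criterion is recorded and reported as an SAE whether or not it is listed.
- **11.9:** state that any serious event judged related to study medication (DCS/placebo) under 12.2 and 12.5.2 counts towards the limit, whether or not it is listed. The same sentence can name the qualifying 12.5.2 grade.

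The cost is one sentence in each section and a short note to sites. The added workload is confined to serious events; minor expected effects stay off the form as the sponsor intended. The limit of two remains the sponsor's choice.

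An allocation check by the outside randomisation unit or the pharmacy (11.2) is optional. It would avoid stopping on placebo events, but an outside party would look up a few codes and the stop would on average come slightly later.

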#### **11.10 Clinical Safety Assessments**

Safety assessments will be performed face-to face at the two days of DCS/ placebo treatment as well as at three using the adverse event questionnaire, as indicated in “Investigational schedule“. The same procedure will be done using telephone assessment at 12 months, and 5-year follow-up.

#### **11.11 Laboratory Assessments**

Patients will be invited to participate in another study involving genotyping samples of blood and saliva, but participation in the present study is not contingent upon participation in the genotyping study.

## **12. Proceedings for Adverse Events**

### **12.1 Definition of Adverse Events**

An Adverse Event (AE) is any unwanted medical occurrence in a subject administered Investigational Medicinal Products (1) and which does not necessarily have a causal relationship with this product. An AE can be any unfavorable and unintended sign, abnormal laboratory finding, symptom or disease temporally associated with the use of IMP, whether or not related to the product. Known side effects of DCS include mild weariness, drowsiness, headaches and tremor. As DCS has been routinely given in far larger doses in studies of tuberculosis, and we only provide small doses for two consecutive days the known side effects recorded in the SPC will not be reported as AEs.

### **12.2 Definition of Adverse Reactions**

Each AE is to be classified by the investigator as related or not related to the IMP. An Adverse Reaction (AR) is a noxious and unintended medical *response* to a medical product related to any dose. For an AE to be an AR the suspected association between the product and the unwanted medical condition should be at least a reasonable *possibility*.

### **12.3 Definition of Serious Adverse Events**

Each AE is to be classified by the investigator as serious or non-serious. Seriousness is not defined by a medical term; it is a result or an outcome. An AE is defined as a Serious Adverse Event (SAE) if it:

- results in death
- is life-threatening
- Requires inpatient hospitalization or prolongation of existing hospitalization
- results in persistent or significant disability/incapacity
- results in a congenital anomaly/birth defect

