#### ***Additional exclusion criteria related to the DCS***

- Pregnancy or breast feeding (the participants are informed that they will have to use contraception the two days when the DCS/placebo is administered. Females will be asked if they are pregnant, and in case of doubt a pregnancy test is provided)
- Renal impairment
- Hypersensitivity to D-Cycloserine
- Porphyria
- Epilepsy

According to the SPC, depression and anxiety should also be exclusion criteria for the administration of DCS. However, in the current study DCS will be administrated in a low dosage for two consecutive days. Several studies have used DCS in the treatment of OCD with the same kind of exclusion criteria, and reported no adverse side effects [8, 9, 62], and studies of other anxiety conditions show the same results [6, 64].

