### **5.3 Withdrawal**

#### ***Criteria for mandatory discontinuation of treatment, including DCS administration:***

- Consent withdrawal by the patient
- High suicide risk according to investigator's judgment or any suicide attempts during the two days administration of the DCS. These patients will be excluded from the study, and taken care of according to the normal procedures of specialist health care in Norway.
- Worsening of OCD symptoms during the two days of DCS-administration, which in the opinion of the investigator requires an adaptation of treatment not compatible with the protocol or requires hospitalization.

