### **12.7.2 Reporting of Serious Adverse Events**

SAEs will be reported by the investigator and sent the principle investigator immediately.

Follow-up information describing the outcome of the SAE and action taken will be reported as soon as it is available. The original SAE form must be filed with the CRF.

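### Section 12.3 limits SAEs to five outcomes with no criterion for a medically important event, so some suicide attempts or seizures would miss immediate reporting and SUSAR classification

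*Protocol*

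**What the plan says.** Section 12.3 has the investigator class every AE as serious or non-serious and gives the basis: "Seriousness is not defined by a medical term; it is a result or an outcome". Five outcomes follow: the event "results in death", "is life-threatening", "Requires inpatient hospitalization or prolongation of existing hospitalization", leaves lasting or significant disability, or causes a birth defect. There is no sixth line for medical judgement.

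The reporting duties differ by class. Under 12.7.1 every AE is recorded on an AE form in the CRF, with no time limit. Under 12.7.2, "SAEs will be reported by the investigator and sent the principle investigator immediately". Section 12.4 applies the SUSAR test to SAEs only, and 12.7.3 attaches the 7-day and 15-day reports to the regulator to SUSARs.

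Three other sections bear on the point:
- Section 5.3 makes "any suicide attempts during the two days administration of the DCS" a ground for mandatory discontinuation of treatment.
- Section 11.9 reads: "The study will be stopped if documentation clearly shows serious side effects related to DCS in two or more patients". It does not use the term SAE or refer to 12.3.
- Section 12.1 keeps known side effects recorded in the SPC from being reported as AEs.

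**The concern.** An investigator who applies 12.3 as written has no ground for calling an event serious because of what it is. The outcome alone decides. That matters in this trial because the protocol itself marks neuropsychiatric harm as relevant. It excludes patients with ongoing or planned suicidal ideation and patients with epilepsy (5.2). It singles out suicide attempts on the dosing days (5.3). It also enrols patients whom the product information would keep out: "According to the SPC, depression and anxiety should also be exclusion criteria for the administration of DCS", and 5.2 explains why the trial departs from this. Participants are outpatients (5.1), so it is plausible that such an event is managed without admission.

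What is at stake is how soon the principal investigator, and through the SUSAR route the regulator, learn of such an event. As written, neither has to be told of it promptly.

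**Working it through.** The protocol states no figure on this point and no arithmetic applies beyond counting criteria. The check sets the sections side by side.

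**Step 1: apply 12.3 to a defined case.** Take a suicide attempt or first seizure on a dosing day that is managed without admission, is not judged life-threatening and leaves no lasting disability.

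| Criterion in 12.3 | Met? |
|---|---|
| Death | No |
| Life-threatening | No |
| Admission or prolonged stay | No |
| Lasting or significant disability | No |
| Birth defect | No |

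Criteria met: 0 of 5. The event is non-serious, and the sentence on medical terms removes the nature of the event as an alternative ground.

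The conditions are all needed. An attempt managed without admission but judged life-threatening is an SAE, and so is a seizure with lasting disability.

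**Step 2: follow the non-serious class through the protocol.**

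| Section | Applies to | Result for the defined case |
|---|---|---|
| 12.7.1 | All AEs | Recorded in the CRF, no time limit |
| 12.7.2 | SAEs | No immediate reporting |
| 12.4 | SAEs at least possibly related to the product | Never assessed as a SUSAR |
| 12.7.3 | SUSARs | 7-day and 15-day clocks cannot start |
| 12.5.1 | All AEs | May be graded severe, but the grade triggers no faster report |

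**Step 3: look for a bridge.** Section 5.3 takes a patient with an attempt on the dosing days off treatment but does not make the event an SAE. No other section adds a medical-judgement criterion.

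**Step 4: read 11.9 both ways.** If its serious side effects are SAEs under 12.3 that are related to DCS, the defined case does not count towards the two patients. If the term is wider, the case may count, but nothing says what else does. The text does not settle which reading applies.

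**Step 5: check the step before 12.3.** Section 12.3 classifies AEs only, and 12.1 withholds SPC-recorded effects from AE reporting. An SPC-listed effect may therefore never be tested for seriousness. The examples in 12.1 are mild weariness, drowsiness, headaches and tremor. The SPC is not at hand, so whether seizure falls under the exclusion cannot be checked.

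**The case against.** The strongest reply is that little would be missed in practice. The capsule is taken in front of the therapist (11.5). Patients stay with the therapist for at least five hours after intake and are in weekly contact for three weeks (section 10). The reason and time of discontinuation are recorded where possible, and an end-of-study visit follows (5.4). Local staff would therefore probably know of a suicide attempt or seizure quickly. That stands. It narrows the gap to the duty to forward the event at once and to test it as a SUSAR, and none of these safeguards supplies either duty.

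It can also be said that the SUSAR loss may be empty, because 12.4 requires the event to be unexpected against the SPC. That is fair: an SPC-listed event would be no SUSAR even if it were serious. For any event that is not listed, the loss remains.

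A reader might infer that 5.3 and 12.3 contradict each other. They do not, because they answer different questions. Section 5.3 decides who stops treatment, and its mandatory list also includes withdrawal of consent. Section 12.3 decides how an event is classed. The fair statement is that nothing links the two for suicide attempts.

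A reader might also infer that every attempt or seizure handled without admission is non-serious. The life-threatening and disability criteria apply without admission, so this does not follow.

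**Conclusion.** The point holds for a defined class of events. Section 12.3 is a closed list of five outcomes with no criterion for an otherwise medically important event. A suicide attempt or seizure that needs no admission, is not judged life-threatening and leaves no lasting disability is non-serious as written. It then misses immediate reporting and cannot enter SUSAR classification. This rests on the text of 12.3, 12.4, 12.7.1 and 12.7.2 and needs no numerical assumption.

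Its size is unknown. The documents give no rate of such events and no share that would meet one of the five criteria. Any percentage missed, or any probability that the threshold in 11.9 is reached late, would rest on an invented input, so none is given.

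It is tempting to conclude that these events also bypass the stopping rule. That follows only if the term in 11.9 means SAEs under 12.3, which the protocol does not say. What is established is that a study-level stopping threshold rests on an undefined term.

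**What to change.** 1. In 12.3, add a sixth criterion: an event that is otherwise medically important in the investigator's judgement, with suicide attempt and seizure named as examples. Qualify the sentence on medical terms so that it does not cancel the new line.
2. In 11.9, state whether the term used means SAEs under 12.3 that are related to DCS or something else. Which meaning is intended is for the sponsor to decide.
3. Reconcile 12.1 with 12.3, so that an event meeting a seriousness criterion is not dropped because the SPC lists it.

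There is no need to make every discontinuation under 5.3 an SAE. That list includes grounds, such as withdrawal of consent, that have nothing to do with seriousness.

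The cost is a short protocol amendment, a matching line on the SAE form and a few more SAE reports in a trial with two dosing days per patient. Dosing, assessments and sample size do not change.
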